### Safety monitoring

During the training session, another research assistant (RA-B), who is a qualified registered nurse, will closely monitor whether the participating students have allergic symptoms such as itchiness, skin rash, etc. If a student has these symptoms, the trainer will inform the responsible teacher immediately. The parents will also be contacted to explain the allergic reaction and advise them to consult their family doctor for detailed assessment. In case the student manifests severe allergic reactions, the trainer and the research assistant will follow the guidelines and emergency care plan on food allergy and anaphylaxis of the schools to call emergency service and provide basic life support to the student immediately.

**Fig. 2 Fig2:**
[figure not shown]
Trial Flow Chart

### Validity and reliability/rigour

To ensure intervention fidelity and adherence, structured observations of a randomly selected session per week will be performed by RA-B. The project team will first develop quality scales to assess the fidelity quantitatively. The quality scales will be session-specific. For the home practice, each participant will have a logbook to record their compliance to the recommended home-practice activities. In addition to the reminder to the participants regarding the home practices by the end of every supervised session, a circular will also be sent to their parents to solicit their help to monitor their children for the home practices every week to increase the treatment adherence.

As both participants in the intervention and control groups are allowed to receive counselling services provided by the school social workers if necessary to handle some emotional/behavioral issues, a record of whom have received the service and how often will be kept to facilitate an interpretation of the study findings.

### Data analysis

IBM SPSS version 23 will be used for statistical analysis. Mean and standard deviation will be reported for continuous variables, i.e. age, types of smartphone functions used and total resilience score. Frequency and percentage will be reported for nominal and ordinal variables. Cronbach’s alpha and intra-class correlation coefficients will be calculated to determine the validities and reliabilities of the two scales: the translated Smartphone Addiction Scale and the Chinese Version of Conner-Davidson Resilience Scale – 25. Independent t-test/Mann-Whitney U test will be used to compare the socio-demographic variables between intervention and control groups. Generalized Estimating Equation model will be used to verify all the hypotheses. The socio-demographic variables will be treated as co-variates to adjust the group means. Results will be reported with 95 % confidence interval. Intention-to-treat analyses will be applied to the independent and dependent variables. Missing data will be handled by replacing the missing values with the item-specific mean. Tests performed will be two-tailed with alpha value set at 0.05. Cohen’s *d*, calculated by taking the difference of the adjusted means between two comparison groups and dividing it by the pooled standard deviation, will be used to estimate the effect size of the treatment.

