**Methods:**

It is an open-label, parallel-group, cluster-randomized controlled trial with repeated measurement analysis. Four primary schools in Hong Kong will be recruited and randomly allocated in a ratio of 1:1 to the intervention/control group. A convenience sample of 240 class level 5 primary school students, 60 from each school, will be recruited. Participants in the intervention group will receive a 12-week MBCP which comprises 90-minute supervised practice at school and daily home practice. Resilience will be measured by Connor-Davidson Resilience Scale – 25 (Chinese version); smartphone behavior will be represented by time spent/day using the smartphone and types of functions used; addictive symptoms will be measured by Smartphone Addiction Scale-Short Version (Chinese Version). Baseline assessment(T0) will be conducted before the intervention starts. Post-tests will be conducted in weeks 4, 8, 12 of the intervention, and 3 months follow-up. Intention-to-Treat analysis will be applied to the variables. Generalized Estimating Equation model will be used to compare differences in resilience scores, smartphone behavior and addiction scores between and within groups, adjusted for socio-demographic factors. *P* < 0.05 with two-tailed test will be regarded as significance.

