
## Methods/Design

### Aim/Objectives

The aim of this study is to examine, through a cluster randomized controlled trial, the effects of a group mindfulness-based cognitive programme on smartphone behavior, resilience and symptoms of smartphone addiction in adolescents.

The primary objective is to investigate the group by the time interaction effects of the group mindfulness-based cognitive programme on resilience, smartphone behavior and the symptoms of smartphone addiction in adolescents.

There are two secondary objectives: (1) To identify adolescents with smartphone addictive symptoms using the Smartphone Addiction Scale-Short Version; (2) To investigate the association of socio-demographic factors, smartphone behavior and resilience with smartphone addiction symptoms in adolescents.

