### Study design and setting

This study will be an open-label, parallel-group, cluster randomized controlled trial with repeated measurement analysis. It will pragmatically evaluate the effects of the mindfulness-based cognitive programme (MBCP) on improving adolescents’ resilience, changing their smartphone behavior and reducing smartphone addictive symptoms as compared with the control group at five measurement points (i.e. baseline (T0), one month (T1), two months (T2), three months (T3) after the programme, three months’ follow up (T4)). The study will be conducted in four primary schools in Hong Kong. The primary schools will be the unit of allocation, and individual participants will be the units of analysis. The intervention group will receive the mindfulness-based programme, and the control group will receive existing counselling services for students with emotional/behavioral problems. (i.e. treatment as usual). Data collection will be started in September 2020. Key aspects of the study design can be found in Fig. 1. We designed and reported this study protocol according to the SPIRIT2013 statement.

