### Outcome measures

#### Demographics

Demographic variables will be gender, age, parents’ educational attainment, parents’ employment status, family structure, parenting skills. Age will be measured in continuous scale; the other variables will be measured in nominal/ordinal scales.

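### Cohen's d is built from means adjusted only for socio-demographics, while the primary test is a group-by-time interaction that includes T0, so the reported effect size and the test can disagree

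*Protocol article*

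**What the plan says.** All references are to the protocol article.

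- **Covariates.** Data analysis: "The socio-demographic variables will be treated as co-variates to adjust the group means". The Methods paragraph of the Abstract agrees: outcomes are compared "between and within groups, adjusted for socio-demographic factors".
- **What counts as socio-demographic.** Demographics: "Demographic variables will be gender, age, parents’ educational attainment, parents’ employment status, family structure, parenting skills". No outcome measured at T0 is on the list.
- **Effect size.** Data analysis defines Cohen's d as "calculated by taking the difference of the adjusted means between two comparison groups and dividing it by the pooled standard deviation". Nothing there subtracts the T0 difference or conditions on it.
- **Primary contrast.** Aim/Objectives: "The primary objective is to investigate the group by the time interaction effects". Study design and setting counts T0 among the "five measurement points (i.e. baseline (T0), one month (T1), two months (T2), three months (T3) after the programme" and a three-month follow-up (T4). Data analysis uses a GEE model for all hypotheses.
- **Baseline comparison.** Data analysis: "Independent t-test/Mann-Whitney U test will be used to compare the socio-demographic variables between intervention and control groups".

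**The concern.** The test and the effect size answer different questions. An interaction with T0 as a level of time asks whether the arms changed differently from baseline. A difference of post-test means adjusted only for family and personal characteristics asks whether the arms differ in level. The two agree when the arms start level, and otherwise differ by the T0 gap.

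A gap is likely here. Four schools, recruited partly on willingness, are allocated by coin toss, and no matching or stratification is described. A reader will take d as the size of the effect that the interaction tested. With an unlucky T0 gap, d could look clearly larger or smaller than that contrast, or point the other way when the true effect is small.

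**Working it through.** **Inputs from the document.** Four schools (two per arm), 60 students per school, ICC 0.01, d = 0.5, two-sided alpha 0.05, Type II error 0.2, 20% dropout.

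**Assumptions.** The ICC applies to T0 scores as well as post-test scores. Rho is not in the document, so a range is shown. The outcome has SD 1.

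**1. The plan's own sample size.** n per arm = 2(1.96 + 0.84)² / 0.5² = 62.8, so 63.
- With 48 evaluable students per school (60 less 20%), the design effect is 1 + 47 × 0.01 = 1.47. Then 62.8 × 1.47 = 92.3, so 93, and 93 / 0.8 gives 117 per arm.
- With 60 per school, the design effect is 1.59. Then 62.8 × 1.59 = 99.8, so 100, and 100 × 1.2 = 120 per arm.

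The stated 120 per arm is reproduced to within 3% or exactly. Neither route takes credit for baseline adjustment.

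**2. Chance T0 difference between arms.** Variance = ICC + (1 − ICC)/60.
- ICC 0.01: 0.01 + 0.0165 = 0.0265. SD 0.163, 95% range ±0.32.
- ICC 0.05 (assumed): 0.05 + 0.0158 = 0.0658. SD 0.257, 95% range ±0.50.

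**3. How much carries into d.** If rho is the same at student and school level, the expected carry-over is rho × T0 gap. For a gap of 0.32 at ICC 0.01:
- rho 0.3: 0.10
- rho 0.5: 0.16
- rho 0.7: 0.22
- rho 0.8: 0.26

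If school effects instead persist unchanged and the within-school correlation is 0.5 (both assumed), the carried fraction is (0.01 + 0.99 × 0.5/60) / 0.0265 = 0.69, giving about 0.22.

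**4. Distance between d and the tested contrast.** At any post-test, difference in level = difference in change + T0 difference. Take a T0 gap of 0.32 in favour of the intervention and rho 0.5.
- True effect 0.5: expected level difference 0.5 + 0.16 = 0.66; expected difference in change 0.66 − 0.32 = 0.34.
- True effect 0: the two are +0.16 and −0.16, so the signs differ.

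**5. Would T0 as a covariate be more precise than the change contrast?** Assume a within-school rho and a slope of 0.5, with school effects fully stable. Change variance = (1 − ICC) × 2(1 − 0.5)/60. Covariate variance = ICC × (1 − 0.5)² + (1 − ICC)(1 − 0.5²)/60.
- ICC 0.01: change 0.0165; covariate 0.0025 + 0.0124 = 0.0149, about 10% smaller.
- ICC 0.05 (assumed): change 0.0158; covariate 0.0125 + 0.0119 = 0.0244, about 50% larger.
- School-level correlation also 0.5: the ratio is (1 − 0.25)/(2 × 0.5) = 0.75, so the covariate is 25% smaller.

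The direction depends on a school-level correlation that the document does not give.

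**The case against.** **Baseline is already handled where it matters.** The interaction subtracts the T0 difference. This stands: a reader might infer that baseline differences pass straight into the trial's main result, but they do not enter the primary test. Even for d, only a fraction of the gap carries over in expectation.

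**Chance imbalance is ordinary sampling error.** Over repeated randomisations d is not biased by it, and the sample size includes a design effect without credit for T0. This also stands. The difference in change is not exempt from chance either: given the T0 gap, its expected error is −(1 − rho) times the gap, which at rho 0.5 is as large as the error in d with the opposite sign. The case for correction is that d should describe the contrast that was tested. It is not that a change score is free of error.

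**Precision is wasted by not using T0 as a covariate.** A reader might infer this from the familiar result for individually randomised trials. Step 5 shows that it does not carry over to four schools. The document does not support a claim of a general gain or loss.

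**Modelling only T1 to T4 would damage other aims.** The Abstract and Sample size calculation also plan within-group comparisons across measurement points. This is a good reason to keep the planned model.

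**The article is condensed.** The visit to which d refers may be fixed elsewhere. But the covariates are named twice and the formula for d is given, so the mismatch lies in what is stated.

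**Conclusion.** The concern holds for the effect size only. As written, d comes from means adjusted for socio-demographics alone, while the primary test compares change from T0. At the protocol's ICC of 0.01 the chance T0 gap has a 95% range of about ±0.32 SD. About ±0.16 of it is expected to carry into d at an assumed rho of 0.5, against a target of 0.5. The range rests on applying the stated ICC to T0 scores with 60 students per school. The carry-over rests on an assumed rho that is equal at both levels, and it is larger if school differences persist. Adjustment for socio-demographics might absorb part of the gap; by how much cannot be judged from the document.

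A minor related point: Demographics puts every variable except age on nominal or ordinal scales. Neither the t-test nor Mann-Whitney suits unordered categories, and neither allows for school. Mann-Whitney does suit the ordinal items taken singly. This affects a descriptive comparison only.

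**What to change.** - Keep the group-by-time GEE as the primary analysis.
- For the resilience and smartphone addiction scores, calculate d and its 95% CI from that model's between-arm difference in change from T0 at each post-test (T1 to T4), divided by the pooled T0 SD. Do not extend this d to the six-category daily-use item, for which a mean difference is not a natural measure.
- If wanted, add a model with the student's T0 value as covariate as a supporting analysis, without claiming in advance that it is more precise.
- Replace the baseline significance tests with a table of characteristics by arm and by school.

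The cost is analysis wording only. T0 is already collected, and the sample size, visits and primary model do not change.

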### Sample size calculation

As it is the first study investigating the effect of the MBCP on smartphone behavior in adolescents, the project team can only decide the predicted intracluster correlation with reference to other studies investigating adolescent behavioral problems. The predicted intracluster correlation of 0.01 is adopted based on studies about smoking prevention and alcohol use in adolescents [55, 56]. 20 % potential dropout/noncompliance rate is considered reasonable. Assuming a Type 1 error of 0.05 and Type II error of 0.2, a total of 240 participants (i.e. 120 in each group, 60 in each school) is required to achieve a medium effect (Cohen’s *d*) of 0.5 [57] for comparing the treatment effect between the two treatment groups and among the measurement points within groups for the three outcomes to be measured – resilience, smartphone behavior and symptoms of smartphone addiction.

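### Item-mean replacement, the only stated rule for missing data, either shrinks the treatment difference or understates its standard error, and distorts Cohen's d

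*Protocol article*

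**What the plan says.** All statements are in the protocol article.

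- **Data analysis, missing data:** "Missing data will be handled by replacing the missing values with the item-specific mean". The article gives no other rule for missing data. It sets no limit on how much may be missing and does not separate skipped items from missed questionnaires. It also does not say over whom the mean is taken.
- **Data analysis, analysis set:** "Intention-to-treat analyses will be applied to the independent and dependent variables". Students who drop out therefore stay in the analysis.
- **Data analysis, model and effect size:** GEE is used for every hypothesis. Cohen's d is the difference in adjusted means divided by the pooled standard deviation. "Tests performed will be two-tailed with alpha value set at 0.05".
- **Sample size calculation:** "20 % potential dropout/noncompliance rate is considered reasonable".
- **Aim/Objectives and Data collection:** the primary objective is the group-by-time effect on three outcomes, measured at baseline and on four later occasions.
- **Smartphone behavior and Demographics:** daily use is recorded in six categories. All socio-demographic covariates except age are nominal or ordinal.

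**The concern.** Taken literally, the rule gives a student who misses a visit the item mean on every item of that questionnaire. The student's own earlier scores, the best guide to the missing ones in a repeated-measures design, are ignored, and the filled-in values then count as observed data.

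Two things follow even under missing completely at random. If the mean is over all students, missing students in both arms get the same value, which pulls the arms together. If the mean is by arm, the difference is preserved, but the imputed values add apparent sample size and no spread. Either way the pooled SD shrinks, and that SD is the denominator of Cohen's d.

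The rule applies to all three outcomes of the primary objective. Because the averaging level is not stated, the same data could give a d below or above the true value, depending on who runs the analysis.

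**Working it through.** **Inputs.** From Sample size calculation: "Assuming a Type 1 error of 0.05 and Type II error of 0.2, a total of 240 participants", split as "120 in each group, 60 in each school"; "a medium effect (Cohen’s *d*) of 0.5"; "The predicted intracluster correlation of 0.01 is adopted". The test is two-sided at 0.05. The SD is scaled to 1. The missing fraction f is an assumption, because the 20% combines dropout with noncompliance; 5% to 30% is shown.

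**The plan's own figure.**
- Per arm before inflation: 2 × (1.96 + 0.8416)² / 0.5² = 62.8.
- Design effect: 1 + 59 × 0.01 = 1.59, giving 99.8.
- Times 1.2 for loss: 119.8, so 120 per arm and 240 in total. The stated figure is reproduced.
- With 96 observed per arm (48 per school, design effect 1 + 47 × 0.01 = 1.47) the same formula gives power 0.815. The planned size thus already carries a 20% loss without imputation.

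**All-student mean** (equal f in both arms, missing completely at random). The imputed value lies midway between the arms.
- Difference = d(1 − f) = 0.5 × 0.8 = 0.40 at f = 20%.
- SD = √[(1 − f) + f(1 − f)(d/2)²] = √(0.80 + 0.01) = 0.90.
- Cohen's d = 0.40 / 0.90 = 0.444.
- With unequal missingness, 30% against 10%, the difference is 0.394, a shrinkage of 21%.

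**Arm-specific mean.** The difference stays at 0.50.
- SD = √(1 − f) = 0.894, so d = 0.5 / 0.894 = 0.559.
- Reported SE = 0.894 × √(2/120) = 0.115; true SE = √(2/96) = 0.144; the ratio is 1 − f = 0.80.
- Type I error = 2[1 − Φ(1.96 × 0.80)] = 11.7%.

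| Missing | All-student: difference | All-student: d | Arm mean: d | Arm mean: SE ratio | Arm mean: type I error |
|---|---|---|---|---|---|
| 5% | 0.475 | 0.49 | 0.51 | 0.95 | 6.3% |
| 10% | 0.45 | 0.47 | 0.53 | 0.90 | 7.8% |
| 20% | 0.40 | 0.44 | 0.56 | 0.80 | 11.7% |
| 30% | 0.35 | 0.41 | 0.60 | 0.70 | 17.0% |

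**Closer to the planned analysis.** A simulated five-visit GEE used 120 students per arm, a within-student correlation of 0.5 (assumed) and an exchangeable working correlation with robust SEs. All post-baseline visits were missing for 20%, means were taken by visit, school clustering was set aside, and 400 runs were made per case. The results are for the group-by-time term at T3:

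| Method | Estimate (true 0.50) | d | Type I error | Power |
|---|---|---|---|---|
| Observed data, no imputation | 0.501 | 0.503 | 4.8% | 94% |
| All-student mean | 0.396 | 0.441 | 5.8% | 86% |
| Arm mean | 0.493 | 0.553 | 9.5% | 95% |

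Under the arm mean the model SE is 0.1285 against an empirical 0.150 to 0.154, so it is about 15% too small. Under the all-student mean the 95% interval covers the true difference 88% of the time. Robust standard errors repair neither problem.

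**Categorical variables.** An average of six response categories is generally not one of them, and a mean has no meaning for nominal covariates. The rule cannot be applied to these as written.

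**The case against.** The strongest defence is that an item-specific mean is naturally a device for skipped items on the 25-item and 10-item scales, and that a condensed article may leave missed questionnaires to a fuller plan. It stands in part: the text does not spell out that a dropout receives item means at every missed visit; that is a literal reading of an unlimited rule. But the rule is stated for missing data in general, next to intention-to-treat. If only skipped items were meant, the text needs to say so.

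Second, the 20% is not a missing-outcome rate. A student who skips sessions or home practice can still fill in questionnaires. This stands, and it is why a range is shown.

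Third, the text names no arm, so the all-student mean is the plainer reading, and there the two-sample test barely moves: z = 0.40 / (0.90 × √(2/120)) = 3.44, against 0.50 / √(2/96) = 3.46 on observed data. It is right that false positives are not inflated on that reading. The estimate, interval and d are still attenuated, and in the simulated group-by-time contrast power fell from 94% to 86%.

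Fourth, the 11.7% belongs to a simple two-sample comparison. This also stands; about 9.5% is the figure nearer the planned contrast.

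**Conclusion.** The point holds: the protocol fixes a poor rule, and this is not a detail merely left for later. If missed questionnaires are filled in as written, an all-student mean shrinks the difference by about the missing fraction and lowers d, with type I error near nominal. An arm-specific mean leaves the difference unbiased, but the SE is too small and d is inflated. The sizes rest on equal missingness in both arms, completely at random, with school clustering set aside. At 5% missing or less the effect is small.

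A reader might infer three stronger things that the documents do not support:

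- **That the estimate, SE and d are all wrong at once.** Each reading damages some of them: the arm-mean difference is unbiased, and the all-student test keeps its size.
- **That one in five outcomes will be missing.** The protocol's 20% includes noncompliance.
- **That the trial's false-positive rate would be 11.7%.** That needs arm-specific means, which the text does not state, 20% missing, and a two-sample test rather than the planned contrast.

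**What to change.** Replace the sentence on missing data in Data analysis with rules that separate two cases.

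1. **Partly completed scale.** Allow item-level substitution only when no more than a stated small share of items is unanswered, using that student's own mean of the answered items. Do not use means for the six-category use question or for nominal covariates.
2. **Missed questionnaire.** Drop mean imputation and analyse all observed visits. Either a likelihood-based mixed model or the planned GEE after multiple imputation using arm, school, baseline and earlier scores would serve; both rest on missing at random. GEE on observed data without imputation performed well above, but only under missing completely at random.
3. **Effect size.** Compute Cohen's d with the SD of observed data.

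The cost is a wording change and slightly more analysis work. Compared with the arm-mean reading, standard errors will be larger. By the plan's own formula no extra recruitment is needed. The change does not settle whether standard errors are valid with only four schools; that is a separate issue.
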